## Abstract

**Background::**

Peripheral facial paralysis (PFP) is a common peripheral neural disease. Acupuncture treatment combined with PFP rehabilitation exercises is a routine method of PFP treatment. This article is to provide a new visual and objective evaluation method for exploring the mechanism and efficacy of acupuncture treatment on PFP, and develop an interactive augmented facial nerve function rehabilitation training system with multiple training models.

**Methods::**

This prospective and observational trial will recruit 200 eligible participants for the following study. In the trial, the laser speckle contrast analysis (LASCA) technology will be applied to monitor the microcirculation of facial blood flow during acupuncture, and real-time monitoring algorithms, data sampling, and digital imaging methods will be conducted by machine learning and image segmentation. Then, a database of patient facial expressions will be built, the correlation between surface blood flow perfusion volume and facial structure symmetry will be analyzed, combined with scale assessment and electrophysiological detection. In addition, we will also explore the objectivity and effectiveness of LASCA in the evaluation of facial paralysis (FP), and the changes in blood flow microcirculation before and after acupuncture treatment will be analyzed.

**Results::**

The standard image of the facial target area with facial nerve injury will be manually segmented by the convolutional neural network method. The blood flow images of the eyelid, cheek, and mandible of the patients’ affected and healthy side will be compared and evaluated. Laser speckle blood flow symmetry Pr and its changes in FP condition evolution and prognosis outcome will be measured, and relevant characteristic signals values will be extracted. Finally, COX regression analysis method is conducted to establish a higher accuracy prediction model of FP with cross-validation based on laser speckle blood flow imaging technology.

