In clinic, individualized acupuncture treatment programs are provided for FP patients according to the severity of FP, the development and change of the condition, different physical conditions, and syndromes. It is urgent to comprehensively evaluate the early stage of FP and grasp the rules of outcome and evolution of FP by noninvasive and dynamic visualization of objective evaluation indicators, which could help explore the mechanism of acupuncture treatment and make clinical acupuncture treatment for FP more predictable, targeted, and proactive.

In recent years, with the internationalization of acupuncture, more and more evidences have shown^[13,14]^ that acupuncture was scientific in treating and preventing certain diseases. Visualization research has led to qualitative changes in western medicine diagnosis and treatment, so we believe that visualization research may also become a breakthrough path for the technological advancement of Chinese medicine.^[15]^ For example, Laser Speckle Contrast Analysis (LASCA)^[16]^ can use the backward dynamic speckle contrast value generated by red blood cell movement in blood vessels to obtain blood flow velocity information and acquire a 2-dimensional high-resolution blood flow distribution image, which is a good indicator for monitoring superficial microcirculation perfusion of the skin and can be applied to PFP research. Our previous study has demonstrated that the blood flow on the affected side of the patient with FP was lower than that on the healthy side by using the technology of LASCA.^[17,18]^ Furthermore, upper and lower extremity stroke rehabilitation training system based on VR technology can be quickly copied to the FP training rehabilitation system. Here, our aim is to expolre the acupuncture mechanism on FP therapy based on LASCA technology combined with deep learning and image segmentation, which can help patients with FP recovery by developing dynamic interactive FP rehabilitation exercises depended on virtual reality technology.

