### Surface blood flow signal collection of face

2.6

PeriCam PSI laser speckle imager (Perimed, Sweden) is applied for surface blood flow signal collection of face. The parameter is set as followings: high resolution, 10 images/s of frequency, the acquisition frequency is 50 Hz, and the sampling density is medium. After that, facial blood perfusion volume is recorded over 3 periods: 5 minutes that the patient lies flat and quietly; the whole process of acupuncture; 5 minutes after needle removal. The evaluation criteria for FP in LASCA are shown in Table 4. When monitoring, the patient is in a supine position, facing directly above, and the laser emission and monitoring head are placed about 25 to 30 cm directly above the patient's face.

**Table 4 T4:** Evaluation criteria for facial paralysis in LASCA.

1. ROI: In machine vision and image processing, machine learning and image segmentation methods are used to automatically divide the facial blood flow image into 6 regions: left and right eye area, left and right cheek area, and left and right jaw area.
2. TOI: In machine vision and image processing, periods of interest are selected. Generally, 3 periods are taken: before acupuncture (5 min), during acupuncture (20 min), after acupuncture (5 min).
3. Pr: Pr = P1 (average blood perfusion volume on the healthy side)/P2 (average blood perfusion volume on the affected side). The closer Pr is to 1, the faster the recovery, the better the curative effect, and the better the prognosis.

LASCA = laser speckle contrast analysis.

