### Nerve electromyogram signal collection using H-B rating scale

2.7

Viking Quest EMG system (Thermo Nicolet Corporation, America) is utilized for nerve electromyogram (EGM) signal collection, and room temperature is maintained at 18°C to 25°C. When the patient is performed with BR of facial nerve, we choose a repetitive waveform to measure the shortest latency of R1 and R2 (Table 5). After that facial nerve function before and after acupuncture intervention is assessed by using H-B rating scale (Table 6).

**Table 5 T5:** Evaluation criteria for facial paralysis in BR.

1. The latency of R1 is 10.0 ± 0.6 ms, when the latency of R1 is ≥2 ms and the difference between the latency of bilateral R1 is ≥2.0 ms, these data can be judged as abnormal.
2. The latency of R2 is 29.3 ± 1.8 ms, and the latency that ≥34 ms can be judged as abnormal.
3. Undetectable or absent signal of R1, R2, and contralateral R2 ′is considered as abnormal.

BR = blink reflex.

**Table 6 T6:** H-B rating scale.

1. Mild: H-B rating scale has a local score of II
2. Moderate: H-B rating scale has a local score of III-IV
3. Moderate to severe: H-B rating scale has a local score of V
4. Severe: H-B rating scale has a local score of VI

H-B = House-Brakmann.

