### Statistical analysis

2.9

SPSS 20.0 statistical software is used for statistical analysis of data (SPSS Inc, Chicago, IL). The correlation between H-B score, BR, and Pr would be analyzed by correlation analysis, the closer the correlation coefficient is to 1 or −1, the stronger the correlation, the closer the correlation coefficient to 0, the weaker the correlation. Radit analysis is adopted to analyze H-B facial nerve function rating scale. In terms of surface blood perfusion signal analysis, statistical analysis is mainly performed on Pr values before and after treatment. Data are expressed as “mean ± SD” and homologous paired sample t test is utilized. COX regression analysis is used to analyze the development of FP and the prediction on model of its prognosis and outcomes. *P* < .05 indicates that the difference is statistically significant, as well as *P* < .01 means that the statistical significance is remarkable.

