
### Establishment of predictive model for prognosis of FP based on LASCA technology and research on rehabilitation training mechanism

3.2

The researchers automatically segregate 3 areas of the eyelid, cheek, and jaw of the affected and healthy side of the patient's facial blood flow image are by machine learning methods and synchronize them. At the same time, the common FP assessment method is incorporated into a unified mathematical statistical model, and the law of change in LASCA symmetry value Pr and the development, evolution, and prognosis of FP is observed. The relevant characteristic signals are extracted, and a COX regression analysis method was adopted to establish a highly accurate prediction model for the prognosis of FP based on LASCA technology, and cross-validation is performed.

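### The Cox prognosis model does not confine its Pr signals to a time before the outcome, so a Pr-change term may show only that Pr moves together with recovery

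*Protocol article*

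**What the plan says.** The Results paragraph of the abstract gives an order of work: "Pr and its changes in FP condition evolution and prognosis outcome will be measured, and relevant characteristic signals values will be extracted", and finally a Cox prediction model with cross-validation. Section 3.2 gives the same order. First "the law of change in LASCA symmetry value Pr and the development, evolution, and prognosis of FP is observed"; next comes signal extraction, after which "a COX regression analysis method was adopted to establish a highly accurate prediction model for the prognosis of FP based on LASCA technology", again with cross-validation. Section 2.9 adds one sentence: "COX regression analysis is used to analyze the development of FP and the prediction on model of its prognosis and outcomes".

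The timings stated elsewhere are few:

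- Section 2.9, on perfusion: "statistical analysis is mainly performed on Pr values before and after treatment".
- Section 2.7, on clinical function: "facial nerve function before and after acupuncture intervention is assessed by using H-B rating scale".
- Section 2.5: treatment is 20 sessions over 4 weeks.
- Section 2.6: within a session "facial blood perfusion volume is recorded over 3 periods", namely 5 minutes at rest, the needling itself, and 5 minutes after needle removal.

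The Introduction describes the need as being to "comprehensively evaluate the early stage of FP and grasp the rules of outcome and evolution of FP", so that treatment can be better planned and targeted.

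**The concern.** A prognosis is made at a moment when the outcome is still unknown, so a prognostic predictor must exist by then. Signals taken from the course of Pr through to the outcome need not meet that condition. If Pr simply mirrors the current state of the nerve, patients who recover will show a larger fall in asymmetry over the 4 weeks because they have recovered. A Cox model given that fall as a covariate will find an association even if nothing measured at the first visit tells recoverers from non-recoverers.

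At stake is what the model may be called. Its accuracy could be reported as prognostic although part of it rests on information that is not available when an early evaluation is made.

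**Working it through.** **1. Is there a plan figure to reproduce?** No. The only planning figure is 200 patients (section 2.2), given without effect size, SD, power or event count. The point does not depend on it.

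**2. Timing of predictor and outcome, side by side.**

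| Element | What the article fixes | Where |
|---|---|---|
| Source of the signals | Pr and its changes, through evolution and outcome | Abstract, Results; section 3.2 |
| Pr in the analysis | before and after treatment | section 2.9 |
| H-B grade | before and after acupuncture | section 2.7 |
| Treatment period | 4 weeks | section 2.5 |
| Outcome after the 4 weeks | none described | – |
| Latest time for a predictor | none described | – |

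On these timings, a change in Pr from before to after treatment and a change in H-B grade from before to after acupuncture cover the same interval. The first value of Pr comes before that interval ends; the change does not.

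**3. Can the mechanism matter? An illustration.** Taken from the article: N = 200 and a window of 28 days (4 weeks). Everything else is assumed:

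- Recovery time T is exponential with median 21 days. The expected share recovered by day 28 is 1 − 2^(−28/21) = 0.60, about 121 of 200.
- Baseline asymmetry A0 = |Pr − 1| is normal with mean 0.3 and SD 0.1, cut off below at 0.05, and independent of T. First-visit Pr thus carries no advance information.
- Asymmetry falls linearly to zero at recovery: A28 = A0 × (1 − min(28/T, 1)).
- Both measurements carry error with SD s.
- Predictor 1 is observed A0. Predictor 2 is D = observed A0 − observed A28.
- One-covariate Cox model, follow-up censored at day 28, 200 data sets for each s.

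| s | C, first-visit Pr | P < .05 | C, Pr change D | P < .05 |
|---|---|---|---|---|
| 0.05 | 0.50 | 6% | 0.66 | 100% |
| 0.10 | 0.50 | 3% | 0.61 | 100% |
| 0.20 | 0.50 | 5.5% | 0.57 | 79.5% |

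The Monte Carlo standard error of a 5% rate with 200 data sets is √(0.05 × 0.95 / 200) = 0.015, so the first-visit rates agree with the nominal 5%. The change D appears predictive at every noise level tried, although no patient's recovery could be foreseen at the start.

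**4. Would cross-validation show it?** No. Held-out patients also have D measured over the window in which they recover. With a single covariate, the fitted risk ranks held-out patients in the same order as D itself as long as the coefficient keeps its sign, so cross-validated concordance would stay close to the values above. Cross-validation guards against overfitting, not against a predictor measured too late.

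**The case against.** The strongest reply is that the article never says which signals enter the Cox model. It measures Pr as well as its changes. Section 2.6 provides a resting recording before needling, so a first value exists. The wording would allow first-visit Pr, the response within the first session, or an early change followed by later recovery, and all of these would be genuinely prognostic. Section 2.9 also gives correlation and the before-after comparison their own methods (correlation coefficients and a paired t test), so the Cox model need not carry the change score. The article states no null hypothesis for the Cox model. The early-evaluation aim comes from the Introduction, and the primary objective in section 2.1 does not name advance prediction. Finally, a condensed article may leave event, time origin and covariate list to a fuller document.

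Most of this stands. It rules out the stronger reading that a reader might infer, that the model tests co-movement and not prediction: the text does not settle that. Missing detail on the event or covariate list is likewise not the point here.

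The sequence itself remains. The abstract and section 3.2 both take the signals from the course of Pr through evolution and outcome, and both call the product a prediction model for prognosis. Someone who follows that sequence as written may enter concurrent change as a predictor, and the one safeguard named would not catch it. Adding first-visit Pr to the same model does not cure this, because the change term still carries later information.

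**Conclusion.** The point holds in a limited form. As described, the predictors of the prognosis model are not confined to a time before the outcome, and the stated timings of Pr and H-B coincide. Any Pr-change term may therefore reflect only tracking of recovery. First-visit Pr is also among the measured quantities, so the model is not necessarily only concurrent.

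The size is unknown. The concordances of 0.57 to 0.66 against 0.50 rest on assumed recovery times, an assumed distribution and measurement error of Pr, and an assumed independence of baseline Pr from recovery. They show the direction and that it can be material; they are not an estimate for this trial. A reader might infer from them that first-visit accuracy will be no better than chance, or that a particular false-positive rate applies. Neither follows: the absence of first-visit information was put in by assumption, and the article supplies no figure to test it. The wording should be changed before the model is built.

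**What to change.** In sections 2.9 and 3.2:

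1. Restrict the predictors of the prognosis model to the first assessment: H-B grade, blink reflex, and Pr from the 5-minute recording before needling in the first session.
2. If early change in Pr is wanted, use a landmark. Change up to a fixed early session predicts only recovery after that session, among patients not yet recovered at it, with the Cox time origin at the landmark.
3. Report the association of Pr change with concurrent recovery separately, and call it tracking and not prediction.

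The first and third changes concern wording and need no new recordings. The landmark needs Pr and recovery status at the chosen session; the article does not say at which sessions these are taken, so this should be checked before one is chosen. The statistical cost is a lower reported accuracy and, for the landmark, the loss of patients who have already recovered by then.

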**Conclusions::**

We use modern interdisciplinary high-tech technologies to explore the mechanism of acupuncture rehabilitation training in PFP. And we will provide evidence for the feasibility of using the LASCA technique as a typing diagnosis of FP in the acupuncture rehabilitation treatment of PFP.

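### The abstract promises evidence for LASCA as a typing diagnosis, but the only stated comparison of Pr with H-B or BR is a correlation, which does not measure correct typing

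*Protocol article*

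**What the plan says.** - **Conclusion.** The abstract (Conclusions) states that the study will supply evidence on the feasibility of "using the LASCA technique as a typing diagnosis of FP".
- **Pr against the reference measures.** Section 2.9 states: "The correlation between H-B score, BR, and Pr would be analyzed by correlation analysis". The coefficient is to be read by its size: "the closer the correlation coefficient is to 1 or −1, the stronger the correlation".
- **Other uses of Pr.** Section 2.9 adds that "statistical analysis is mainly performed on Pr values before and after treatment", by a paired t test. Section 3.2 plans Cox regression to "establish a highly accurate prediction model for the prognosis of FP based on LASCA technology, and cross-validation is performed".
- **What Pr is.** Table 4 in section 2.6 defines Pr as mean perfusion on the healthy side divided by that on the affected side. It reads Pr as follows: "The closer Pr is to 1, the faster the recovery, the better the curative effect, and the better the prognosis". It gives no cut-off or band of Pr for any type.
- **Candidate types.** Table 6 in section 2.7 sets four ordered severity classes, for example "Moderate: H-B rating scale has a local score of III-IV". Table 3 in section 2.3 sets four TCM syndromes, which have no order. Table 5 gives normal/abnormal rules for BR. The article does not say which of these the typing refers to.

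**The concern.** A correlation coefficient describes how closely two measures move together across a group. It does not say how often a patient would be put in the right class. That depends also on where the class boundaries lie and how many patients fall in each class. A moderate or fairly strong correlation can go with frequent misclassification. As written, the study could finish with a respectable coefficient and no result on the property named in its conclusion. If the types are the TCM syndromes, the gap is wider: Pr enters no stated analysis with them, and a coefficient would depend on arbitrary numbers given to unordered categories.

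**Working it through.** **1. Stated analyses against the conclusion**

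| Analysis | Question it answers | Tests assignment to a type? |
|---|---|---|
| Correlation of H-B, BR and Pr (2.9) | association | no |
| Correlation of perfusion with facial symmetry (abstract, Methods) | association | no |
| Ridit analysis of H-B (2.9) | distribution of H-B grades | no; Pr not involved |
| Paired t test of Pr (2.9) | change with treatment | no |
| Cox model, cross-validated (abstract, 2.9, 3.2) | prognosis | no; its target is a future outcome |

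The article states no sensitivity, specificity, AUC, classification table or agreement statistic for Pr against a reference type.

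**2. What a given correlation implies for typing (illustration)**

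The article gives no expected correlation and no class shares, so there is no figure of its own to reproduce. The following are assumptions:
- Pr, suitably scaled (X), and latent severity (Y) are bivariate normal with correlation r.
- Y is cut into four ordered classes, as in Table 6.
- Class shares are 25/25/25/25, 30/40/20/10 or 20/50/20/10 percent.

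Cut-points are c = Φ⁻¹(cumulative share). For 20/50/20/10 they are −0.84, 0.52 and 1.28.

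Given X = x, the probability of the class between c₁ and c₂ is Φ((c₂ − r·x)/√(1 − r²)) − Φ((c₁ − r·x)/√(1 − r²)). The best possible rule picks the class with the highest probability. Weighted kappa uses cut-offs on X that reproduce the true class shares. All results in the table come from simulation.

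| r | Class shares | Best rule, % correct | Always naming the largest class | Linear-weighted kappa | AUC, mild v. rest |
|---|---|---|---|---|---|
| 0.5 | 25/25/25/25 | 39 | 25 | 0.32 | 0.74 |
| 0.5 | 30/40/20/10 | 46 | 40 | 0.31 | 0.74 |
| 0.5 | 20/50/20/10 | 52 | 50 | 0.30 | 0.75 |
| 0.7 | 25/25/25/25 | 48 | 25 | 0.48 | 0.84 |
| 0.7 | 30/40/20/10 | 53 | 40 | 0.47 | 0.84 |
| 0.7 | 20/50/20/10 | 58 | 50 | 0.46 | 0.85 |

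Here r is the correlation with latent severity. The rank correlation with the observed class is a little lower: about 0.45 when r = 0.5, and about 0.65 when r = 0.7.

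**3. Check in closed form**

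For two classes split at the median, sensitivity = specificity = 1/2 + arcsin(r)/π.
- r = 0.5: 0.5 + 0.524/3.142 = 0.67.
- r = 0.7: 0.5 + 0.775/3.142 = 0.75.

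These agree with the simulated 0.67 and 0.75. With only two types, r = 0.7 still misplaces about one patient in four.

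**4. If the types are the TCM syndromes**

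No calculation applies. Table 3 lists unordered categories, so a correlation with Pr has no defined value until each syndrome is given a number, and it changes with that choice.

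**The case against.** - **Only feasibility is claimed, once, in the abstract.** True, and the primary objective in section 2.1 does not mention typing. Association with H-B and BR is a reasonable first step. This softens the point, but the feasibility of typing still needs some measure of correct assignment.
- **A significant but trivial correlation would be passed off as support.** A reader might infer this, because at n = 200 any |r| of at least 1.972/√(198 + 1.972²) = 0.139 gives two-sided P < .05. The document does not support it. Section 2.9 reads the coefficient by its size, and its P-value rule is worded for a difference. By the plan's own reading, 0.139 is weak.
- **Pr would type worse than guessing.** With 20/50/20/10 shares and r = 0.5, a rule that matches the class shares gets 46% right, below the 50% from calling everyone moderate. That comes from the rule: the best one gets 52%. Quadratic-weighted kappa in this case is 0.43 against 0.18 unweighted, so the choice of measure matters.
- **H-B is a poor yardstick.** The Introduction criticises its utility and reliability. Disagreement with H-B classes would therefore not by itself refute typing by Pr. This limits how a classification result may be read; it does not make correlation with the same scale better evidence.
- **Section 3.2 refers to a unified model, and the article is condensed.** A fuller plan may contain more. But the target stated in 3.2 is prognosis, and the mismatch lies between a conclusion and analyses that the article itself states.

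**Conclusion.** The point stands in a limited form. The stated analyses can show that Pr is associated with H-B and BR, changes with treatment and predicts outcome. They cannot show that it assigns patients to the right type, and the type is not identified. Under the assumed model, a correlation of 0.5 means about 39% to 52% correctly typed at best, linear-weighted kappa about 0.3 and mild-versus-rest AUC about 0.75. At 0.7 the figures are about 48% to 58%, 0.47 and 0.84. They rest on bivariate normality and on assumed class shares, and they forecast nothing about Pr. They do not show that typing by LASCA would fail, only that a correlation leaves the question open.

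**What to change.** Choose one of two changes.

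1. **Narrow the conclusion.** Limit the abstract's sentence to the association of Pr with H-B and BR and to prognosis, within confirmed unilateral facial paralysis. The cost is one sentence.
2. **Keep the typing claim and test it.** Name the reference type and add a classification analysis to section 2.9. For the Table 6 classes, report the AUC of pre-needling Pr at each class boundary with a 95% confidence interval, and a cross-validated weighted kappa with the weights fixed in advance. State that H-B is itself an imperfect reference. The same analysis for BR, as a benchmark, is optional. If TCM syndrome is meant, use a method for unordered classes instead of a correlation.

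The second option is a small extra analysis of data already planned, with no added participants or procedures.
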